## Renal function

Studies have shown that early after transplantation, glomerular filtration rate (GFR) was consistently higher in patients receiving SRL-MMF than CNIs-MMF. However, recently, Larson et al. reported that the iothalamate clearance at 1 month was higher in the SRL-MMF than in the TAC-MMF group ( $67 \pm 18$  mL/min vs.  $58 \pm 17$  mL/min). But, this difference was lost at 1 year due to unexpected loss of GFR in the SRL-MMF group.

## CAN

Flechner et al. showed that at 2 years a third of patients treated with SRL-MMF had normal biopsies while 79.2% of patients treated with CsA-MMF had histological evidence of CAN. Moreover, Larson et al. observed that, although renal function was similar, chronic vascular damage was significantly lower in the SRL-MMF than in the TAC-MMF combination (26% vs. 43%). Thus, the SRL-MMF combination as maintenance immunosuppression is associated with a reduction in chronic renal damage in the majority of studies performing protocol biopsies. However, whether histological benefit depends on avoiding CNIs or arises from the direct antifibrotic effect of the SRL-MMF combination is not known.

## Adverse events

SRL and MMF are potent immunosuppressants that have antiproliferative properties and interfere at different steps of the cellular cycle. Each drug is associated with a particular profile of side effects; some of them could be amplified or minimized when SRL and MMF are co-administered (Figure 2).

[figure not shown]

**Figure 2: Adverse events in SRL-MMF combination**

**Bone marrow suppression:** Both drugs are associated with bone marrow suppression, in fact, in both SRL- and MMF-treated patients, the incidence of leukopenia (leukocytes < 3000 per mm^3) and thrombocytopenia (platelets < 90000 per mm^3) was 20–45%. Anemia is perhaps the paradigm of adverse event amplification. Anemia is increasingly recognized as an important posttransplant comorbidity. Posttransplant anemia has multifactorial etiology, such as poor graft function, iron deficiency and some antihypertensive and immunosuppressive medications. MMF by its inherent mechanism of action was early recognized as a potent bone marrow suppressor and is considered an independent predictor of posttransplant anemia, which seems to be dose-dependent. More obscure and ill-defined are the mechanisms of SRL-related anemia. In a recent paper, Augustine et al. showed a clear association between posttransplant anemia and SRL (57% of SRL-treated patients had anemia 12 months after transplantation). The authors postulate that SRL induces an erythropoietin-resistance state by inhibiting erythropoiesis at the level of the erythropoietin receptor, since the mTOR downstream pathway is critical for erythroid cell replication. This feature may be important after transplantation, when the patient needs to recover from postsurgical anemia.

**Gastrointestinal side effects: SRL and MMF pharmacokinetic interaction:** These adverse events are mostly related to MMF toxicity although SRL was also described as a cause of intestinal ulcerations and diarrhoea. In fact, painful oral ulcers are frequently reported in patients treated with SRL-MMF. On the other hand, Kreis et al. reported higher incidence of diarrhoea in SRL-MMF than in CsA-MMF (38% vs. 11%). Interestingly, these authors' pharmacokinetic studies showed that, with an equivalent MMF dose, MPA trough levels were significantly higher in SRL- than in CsA-treated patients. Elsewhere, a pharmacokinetic explanation of these findings was provided: that CsA decreases biliary excretion of MPA glucuronide by a mechanism that involves inhibition of multidrug resistance-associated protein 2, blocking an important mechanism for maintaining MPA concentration. In a recent paper, Cattaneo et al. found that SRL but not CsA treated patients showed a second peak consistent with the enterohepatic recirculation of MPA. The result is that nearly half a dose of MMF is usually required to maintain adequate MPA concentration in CsA-free regimes. However, it should be pointed out that the value of trough MPA concentration for MMF therapy still has to be determined.

**Lymphocele and wound-healing complications:** The use of SRL and MMF has been described as causing cicatrization problems. This kind of adverse event is poorly defined in most studies and its incidence could range between 5% and 40%. However, all immunosuppressive agents inhibit to some extent wound healing, especially steroids. Although controversial, these results suggest that in the SRL-MMF combination, experience is critical in making refinements that lead to a significant improvement in the postsurgical period. All these observations raise the question of when to start SRL after transplant surgery.

## **MATERIAL AND METHODS**

### **PATIENTS**

Total number of patients to be studied will be 60.

### **INCLUSION CRITERIA**

- Willing to sign informed consent
- Adult renal transplant recipients of either sex over the age of 18 years
- Undergone denovo live donor renal transplantation at least 2 months prior to enrolment
- Receiving CNI based maintenance regimen after transplantation
- Serum creatinine  $\leq 1.2$ mg/dl and proteinuria  $< 800$ mg/day

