## INTRODUCTION

Since the early 1980s, the standard approach to immunosuppression in transplant recipients has involved the use of calcineurin inhibitors (CNI) such as cyclosporine (CsA) and tacrolimus. CNIs reduce the number of acute rejection episodes and enhance short-term allograft survival. However, the greater benefit appears to be a decrease in the number of acute rejections during the first months after transplantation. Progressive chronic nephrotoxicity is a major toxic effect of CNI in the long term and is associated with mild-to-moderate renal dysfunction. Death from cancer or cardiovascular diseases with a functioning graft is also a major cause of late graft loss. The balance between preventing immunological allograft failures, avoiding over immunosuppression and managing nephrotoxicity is therefore still an unresolved issue. The introduction of immunosuppressive drugs such as mycophenolate mofetil (MMF) and sirolimus (SRL) has strengthened the case for minimizing the use of CsA. SRL is an antifungal macrolide that displays potent antiproliferative activities that produce immunosuppressive effects. Binding of SRL to the intracellular immunophilin FKBP12 blocks the activity of the mammalian target of rapamycin (mTOR) with potent inhibition of downstream signal ligand progression from the G1 to the S phase of the cell-cycle. SRL has been shown to reduce the incidence of acute rejection after renal transplantation, without appearing to cause significant inherent nephrotoxicity in most animal and human studies. However, when combined with CNI therapy, renal function often worsens as a result of potentiated nephrotoxicity. SRL has therefore been used as a primary immunosuppressant in CNI-free regimens. Together with anti-CD25 antibody or anti-thymocyte globulins, MMF and steroids, these regimens have provided comparable 1-year patient and graft survival, and incidence of acute rejection episodes. Furthermore, renal function was also significantly better in the CsA-free group and did not tend to worsen during the first year after transplantation. However, early use of SRL after transplantation has been demonstrated to be associated with various complications including lymphocele, prolonged delayed graft function (DGF), delayed wound healing and by a slight increased incidence of acute rejection. This study could help in evaluating the ideal dose, trough blood level, safety and benefits of conversion to Sirolimus based regimen from CNI based regimen in Indian patients.

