### ***Switch to SRL in maintenance phase***

In recently published CONCEPT study, patients were converted to SRL at 3 months or maintained on cyclosporine, both in combination with MMF. In this study, patient and graft survival were not significantly different, but patients on the SRL regimen had improved renal function at the end of 1 year. The CONVERT trial findings indicated that improved graft function occurs in patients with eGFRs above 40 ml/min and a urine protein:creatinine ratio < 0.1 when they are randomly switched from CNIs to SRL 6 to 120 months post transplant period. In recently published Spare the Nephron trial, random switch over to SRL from CNIs 30 to 180 days post transplant resulted in similar measures of renal function but with fewer deaths and a trend to less Biopsy proven acute rejection and graft loss over 2 years of study period.

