### **STUDY METHOD**

This will be an open label, prospective, randomized, two arm study to be conducted in renal transplant recipients who have undergone renal transplant >2 months prior to enrollment. Renal transplant recipients who had undergone live donor renal transplantation and are on CNI based maintenance regimen will be screened for inclusion and exclusion criteria. Informed consent will be taken after explaining the objectives and procedures of the trial from all the patients who agree to participate in the study. Subjects who satisfy all inclusion and exclusion criteria will either continue with existing CNI regimen or converted from CNI based regimen to sirolimus with CNI withdrawal.

At baseline patient's past, family, medical, transplant and medication history will be enquired and relevant findings will be recorded in the CRF. Patient's general and physical findings will be recorded. Baseline laboratory investigations including CBC, electrolytes, fasting blood sugar, renal profile, SGOT, SGPT, Lipid profile, urine analysis and 24 hrs urine test for urine proteins will be done and recorded. Baseline and subsequent GFR will be calculated by MDRD method. CNI dose and blood levels of all the patients will be recorded at baseline. Subsequently the patients will be randomized either to CNI group who will continue with existing dose or to Sirolimus group. Patients allocated to Sirolimus group, will be initiated

with a loading dose of 6mg for 2 days and later the dose will be adjusted to achieve a blood level of 8-15ng/ml. The CNIs in sirolimus group will be discontinued 12 hrs prior to initiating Sirolimus. Later, in CNI or sirolimus group the dose of individual drugs will be titrated as per target blood level and clinical response. Concomitant immunosuppressants like Mycophenolate mofetil (MMF) and steroids will be continued as per the clinical practice. All the drugs for any pre-existing or co-existing illness will be allowed unless those drugs are contraindicated. All the subjects will be assessed at regular intervals and at the end of study period of 6 months. Relevant laboratory investigations will be done at defined intervals and all the investigations done at baseline will be repeated at the end of study period.

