FoxP3+ T regulatory cell population will be analyzed at baseline, and at 1, 3 and 6 months after enrolment. By flowcytometry using anti-human allophycocyanin (APC) conjugated-CD4 antibodies, phycoerythrin (PE)-Cy7 conjugated-CD25 antibodies (BD Biosciences) and Alexa-fluor 488 conjugated-FoxP3 antibodies (BD Biosciences) on BD FACS Aria II (BD Biosciences). A total of 20000 events will be acquired, and CD25+ FoxP3+T cells will be counted using FACS DIVA 6.0.

1: 1 randomization will be done with the help of a computer generated random number table, and allocation concealment will be achieved by opaque sequentially numbered sealed envelopes. The response of the patient to the therapy will be in terms of renal function assessment. The primary analysis will be two-sided independent sample t-test for difference of means for GFR estimation by MDRD method.

A sample size of at least 25 patients per treatment arm will provide at least 80% power based on the assumption of an effect size (difference of GFR estimates between two treatment arms) of 8 mL/min and S.D. as 10 mL/min

The secondary endpoints will be:

- Acute rejection
- Patient and graft survival at 6 months,
- Incidences of hyperlipidemia, NODM, hypertension and infectious complications
- Regulatory T-cell population

All patients will be followed up at 15, 30, 60, 120 and 180 days. All investigations required to determine the primary and secondary end points will be performed. Sirolimus levels will be determined at 5, 12, 30, 60 and 120 days in patients randomized to sirolimus arm whereas those on tacrolimus will have measurements at 30, 60 and 120 days.

The target trough levels are as follows:

- Sirolimus: 8-15ng/ml
- Tacrolimus: 8-10 ng/ml upto mo 3, 6-8 ng/ml thereafter
- Cyclosporine: 200-300 ng/ml upto mo 3, 150-250 ng/ml thereafter

All unexplained episodes of graft dysfunction will be investigated by biopsy. Acute rejection will be treated as per standard protocol.

Variables will be presented as mean  $\pm$  SD and categorical variables as percentages. Appropriate statistical studies will be used for analysis of results. Two-tailed P-value  $<0.05$  will be considered significant.

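### Time since transplant has a 2-month floor and no ceiling, and the unstratified list and unadjusted primary t-test ignore it: a modest, cheaply avoided loss of precision, not a bias

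*Protocol*

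**What the plan says.** The inclusion criteria (Protocol, Inclusion Criteria) require "Undergone denovo live donor renal transplantation at least 2 months prior to enrolment". The Study Method section repeats the floor for recipients "who have undergone renal transplant >2 months prior to enrollment". Neither place gives an upper limit, and none of the exclusion criteria supplies one.

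On allocation, Study Method states "1: 1 randomization will be done with the help of a computer generated random number table", concealed in sealed envelopes. No stratification factor or blocking is mentioned. On analysis it states: "The primary analysis will be two-sided independent sample t-test for difference of means for GFR estimation by MDRD method". No covariate is named. These are choices made in the protocol itself, and stratification cannot be added once patients have been randomised.

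Time since transplant will be known for every patient: it must be checked for eligibility, and the Study Visit Plan takes the transplant history at visit 0.

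**The concern.** A patient nine weeks after transplant and one nine years after transplant are equally eligible and enter the same comparison of means. The protocol's background gives reason to think that time might matter. The Introduction says that the main CNI benefit is "a decrease in the number of acute rejections during the first months after transplantation". The section on switching to sirolimus in the maintenance phase describes three conversion trials by their windows, and their renal results differ.

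If time since transplant predicts GFR, leaving it out of the model puts its variance into the error term. With a small unstratified trial, the arms may also differ in their mix of early and late patients by chance. Finally, a reader of the result would not know which stage after transplant it describes unless the enrolled distribution is reported.

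**Working it through.** **Inputs from the protocol.** Difference 8 mL/min, SD 10 mL/min, two-sided 0.05, at least 80% power, at least 25 per arm (Study Method). Total 60 patients at 1:1, so 30 per arm (Patients).

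**Inputs assumed.** The documents give neither the share of early patients nor the GFR variance explained by time. I take an early share of 30-50% and 5-15% of variance explained.

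**1. The stated sample size reproduces.** n per arm = 2(1.960 + 0.842)² × 10² / 8² = 24.5, rounded up to 25. Power at 25 per arm is 80.7% by the normal approximation and 79.1% by the noncentral t. There is no arithmetic error here.

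**2. Power of the planned test at 30 per arm.** Standard error = 10 × √(2/30) = 2.58 mL/min; noncentrality = 8 / 2.58 = 3.10; 58 degrees of freedom. Power is 86.1%.

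**3. Power with adjustment.** The residual SD becomes 10 × √(1 − R²), with 57 degrees of freedom after one covariate.

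| Variance explained by time | Residual SD | Power, 30 per arm |
|---|---|---|
| 0% | 10.00 | 86.1% |
| 5% | 9.75 | 87.8% |
| 10% | 9.49 | 89.4% |
| 15% | 9.22 | 91.0% |

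In patients, the gain is 30/0.95 = 31.6 to 30/0.85 = 35.3 per arm, or about 2 to 5 more per arm. The degree of freedom costs almost nothing (86.14% to 86.12% at R² = 0). The table takes time as balanced between arms. Without stratification, chance imbalance in the covariate inflates the variance by about 28.5/28 = 1.018 on average (treating log time as roughly normal). That amounts to 29.5 instead of 30 per arm, and power of about 85.5% if time explains nothing.

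**4. Chance imbalance.** For two independent binomial counts with n = 30, the probability that the early shares differ by 20 percentage points or more is 12.0% at a true share of 30% and 15.5% at 50%.

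**5. What that imbalance does to GFR.** If a binary early/late factor with share p explains R² of a variance of 100, the gap between groups is g = √(100 R² / (p(1 − p))), and a 20-point imbalance shifts the treatment difference by 0.2g.

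| p | R² | g (mL/min) | Shift (mL/min) |
|---|---|---|---|
| 0.5 | 5% | 4.5 | 0.9 |
| 0.3 | 5% | 4.9 | 1.0 |
| 0.5 | 15% | 7.7 | 1.5 |
| 0.3 | 15% | 8.5 | 1.7 |

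The shift is at most about two thirds of one standard error (1.7 / 2.58) and about a fifth of the planned difference (1.7 / 8).

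**The case against.** The strongest reply is that nothing here is invalid. Randomisation makes the unadjusted test valid, chance imbalance is already in its standard error, and the same 12-16% imbalance risk applies to any unstratified factor of that prevalence. The trial enrols 5 per arm more than its own calculation needs. The creatinine and proteinuria limits, live donors only, and the exclusion of second transplants already narrow baseline function. A wide window is a legitimate choice: one of the cited trials ran from 6 to 120 months. All of this stands, and it keeps the point small.

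A reader might go further and infer that the protocol's evidence ties both the renal benefit and the rejection risk to timing. The documents do not support that.

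- **Renal benefit.** Function improved after conversion at 3 months and also at 6 to 120 months, and the later result is conditioned on eGFR and proteinuria, not on time. The trial in which "random switch over to SRL from CNIs 30 to 180 days post transplant resulted in similar measures of renal function" has a window that contains the 3-month point, so the contrast between those two trials cannot be put down to timing alone.
- **Rejection.** The same sentence goes on to report fewer deaths and a trend to less biopsy-proven rejection. The excess rejection described elsewhere concerns early or de novo sirolimus; the 2-month floor rules out de novo use and the first two months.
- **Trough targets.** The change in CNI targets at month 3 would show that care depends on time since transplant only if month 3 counts from transplant, and the protocol does not say.

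A reader might also fear a diluted effect. If only 75% or 50% of the patients gained the 8 mL/min, the pooled difference would be 6 or 4 mL/min and power at 30 per arm about 63% or 33%. No figure in the documents supports such a split, and adjusting for time as a main effect would not cure it.

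**Conclusion.** The point holds as a matter of efficiency and description. Eligibility is open-ended, the list is not stratified by time since transplant, and the primary test ignores it. The consequences are some lost precision and exposure to chance imbalance; there is no systematic bias and no inflation of type I error.

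The size is modest: roughly 2 to 5 points of power, and a shift of 0.9-1.7 mL/min when a 20-point imbalance occurs. Both rest on the assumed 5-15% of variance explained, and the shift and imbalance figures also rest on the assumed 30-50% early share. If time explains little, adjustment gains nothing and costs well under one point of power. The change is worth making because it is specific and nearly free, not because the planned analysis is unsound. An upper limit on time since transplant is a trade-off for the sponsor, not a requirement.

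**What to change.** 1. Replace the primary t-test with a linear model of 6-month MDRD GFR on treatment and log time since transplant (taking the end of the 6-month study as the primary time point), and report the adjusted difference with its confidence interval.
2. Preferably stratify the envelope list by one pre-stated cut-point in time since transplant, in permuted blocks within each stratum.
3. Report the distribution of time since transplant by arm and use it when stating to whom the result applies. Neither of the first two steps makes the result specific to one conversion window. A table of rejection by time group is optional and, with 60 patients, descriptive only.
4. State whether month 3 in the CNI trough targets counts from transplant or from randomisation.

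The cost is one factor on the list, one degree of freedom in the model and a few lines of text. No new data are needed. Setting an upper limit instead would define the window but would narrow recruitment.

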### **EXCLUSION CRITERIA**

- Pregnant, nursing mothers or women of childbearing potential without an effective method of birth control.
- Renal transplant recipients who had episodes of acute rejection, delayed graft failure or signs of graft failure and were unable to achieve serum creatinine  $\leq 1.2$ mg/dL.
- Patients suffering from any malignancy requiring immediate surgery, ongoing chemotherapy or radiation.
- Patients suffering from any acute systemic infection within 30 days prior to enrolment.
- Use of any investigational drug upto 4 weeks prior to enrolling in the study.
- Patients requiring second renal transplantation.
- Patients with untreated hypercholesterolemia defined as having total cholesterol  $> 200$  mg/dl, triglycerides  $> 300$ mg/dL.

- Patient is leukopenic defined as WBC count < 3000 cells/ $\mu$ L or thrombocytopenic defined as platelets < 10000 cells/ $\mu$ L.
- Patient has significant liver disease defined as having during the past 30 days continuously elevated SGOT and or SGPT levels greater than 3 times the upper value of normal range.
- Patients suffering from severe diarrhoea, vomiting, GI malabsorption or active peptic ulcer disease.

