| Vital Parameters
(PR, BP, Fluid Intake and Urine output)                                                                                                                                      | X        | X                   | X                   | X               | X                | X                |
| Blood tests
CBC, Serum creatinine, Blood urea, electrolytes, Blood sugar, lipid profile, SGOT, SGPT, Urine for routine analysis, 24hrs urine for protein and Urine protein to creatinine ratio | X        | -----               | -----               | -----           | X                | X                |
| Therapeutic drug monitoring                                                                                                                                                                       |          |                     |                     |                 |                  |                  |
| i. Rapacan group                                                                                                                                                                                  | ----     | X                   | X                   | X               | X                | X                |
| ii. CNI Group                                                                                                                                                                                     | ----     | -----               | -----               | X               | X                | X                |
| Dose titration of                                                                                                                                                                                 |          |                     |                     |                 |                  |                  |
| i. Rapacan                                                                                                                                                                                        |          | X                   | X                   | X               | X                | X                |

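### The platelet exclusion of < 10000 cells/µL appears to be a numerical error and admits markedly thrombocytopenic patients to a marrow-suppressive regimen

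*Protocol*

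**What the plan says.** One bullet under Exclusion Criteria in the protocol carries both blood-count limits. For white cells it reads "Patient is leukopenic defined as WBC count < 3000 cells" per µL, and for platelets "thrombocytopenic defined as platelets < 10000 cells" per µL. Nothing else in the inclusion or exclusion lists mentions platelets or bleeding.

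The literature review, under Adverse events (bone marrow suppression), uses the same two terms when it reports toxicity in cited studies: "leukopenia (leukocytes < 3000 per mm"³ and "thrombocytopenia (platelets < 90000 per mm"³. It puts the incidence of these events at 20–45% in treated patients and states of sirolimus and MMF: "Both drugs are associated with bone marrow suppression".

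Under Study Method, patients allocated to sirolimus start "with a loading dose of 6mg for 2 days" and are then titrated to 8–15 ng/ml. On background therapy the text says: "Concomitant immunosuppressants like Mycophenolate mofetil (MMF) and steroids will be continued as per the clinical practice".

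In the Study Visit Plan, the blood-test row, which begins "CBC, Serum creatinine, Blood urea, electrolytes, Blood sugar, lipid profile, SGOT, SGPT", is marked at visits 0, 4 and 5 and dashed at visits 1, 2 and 3.

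**The concern.** An eligibility limit is applied at screening exactly as it is written. At 10000/µL the criterion would let through, for example, a patient with 20000/µL, whom the protocol's own background would call thrombocytopenic. Such a patient could be loaded with sirolimus on top of MMF, two drugs that the protocol says suppress the marrow.

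Conversion may also increase the second exposure. The review's section on gastrointestinal effects reports higher mycophenolic acid troughs with sirolimus than with cyclosporine at the same MMF dose, and says that roughly half the MMF dose usually suffices without cyclosporine. The protocol sets no MMF reduction at conversion. It also has no platelet-based rule for dosing or withdrawal. The entry limit is thus the main written safeguard for platelets.

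**Working it through.** The disputed figure is a stated cut-off, not a derived one, so the check is a comparison of the document's own numbers.

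**Units.** 1 mm³ = 1 µL, so the limits compare directly.

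| Count | Adverse events review | Exclusion Criteria | Ratio |
|---|---|---|---|
| White cells | < 3000 per mm³ | < 3000 per µL | 3000 / 3000 = 1 |
| Platelets | < 90000 per mm³ | < 10000 per µL | 90000 / 10000 = 9 |

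**If a zero was dropped** (an assumption): 100000 / 10000 = 10.

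**Band admitted.** Counts of at least 10000 but below 90000/µL are thrombocytopenic in the review's terms and are not excluded. If the intended limit was 100000, the band runs from 10000 to just under 100000/µL.

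**Whether another rule closes the gap.** The remaining criteria cover pregnancy, rejection and graft function, malignancy, infection, investigational drugs, second transplants, lipids, liver enzymes and gastrointestinal disease. None would catch a low platelet count, and there is no general exclusion at the investigator's discretion. Study Method then sends everyone who meets the criteria to one arm or the other.

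**Next scheduled blood count.** Visits 1 to 3 (days 0–14, 15–30 and 60) are dashed. The next mark is visit 4, at day 120 ± 7: 120 − 7 = 113 to 120 + 7 = 127 days.

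**Effect on the primary analysis.** The sample size uses a difference of 8 mL/min and an SD of 10 mL/min. The normal approximation with two-sided α = 0.05 and 80% power gives n = 25 per arm, with power 0.807 at that n, in line with the protocol. The platelet limit is not an input.

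**The case against.** - **The review is background.** Its 90000 describes adverse events in cited studies and is not a rule of this trial. An adverse-event limit and an exclusion limit need not agree. This stands, and it means that the document does not strictly contradict itself. It does not make 10000 a sound limit for a regimen that the same document calls marrow-suppressive.
- **The two clues point to different values.** The white-cell match suggests that 90000 was meant; the missing zero suggests 100000. If 100000 was meant, the white-cell match carries less weight. This also stands: the intended figure cannot be settled from the text. Either value leads to the same conclusion about 10000.
- **The monitoring gap may be less firm than the table suggests.** The blood-test row bundles the blood count with creatinine, sugar and lipids. Study Method promises every test needed for the endpoints at days 15, 30, 60, 120 and 180, and relevant laboratory tests at defined intervals. A blood count might be done when assessing infectious complications, which are a secondary endpoint. That is possible, but platelet count is not an endpoint and no text requires an earlier count. The gap of 113 to 127 days describes the visit table, not what every site will do.
- **Other safeguards exist.** The blood count is known at baseline, study drugs are titrated to clinical response as well as blood level, concomitant drugs may be adjusted and adverse effects recorded at visits 1 to 5, and patients may be withdrawn if a concomitant disease makes continuing unsafe. These help after entry but do not replace an entry limit.
- **A misread digit.** The figure appears once, in text read by machine. Nothing in the passage suggests a misreading, but the source page is quick to check.

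**Conclusion.** The criterion is wrong as written and should be corrected. The platelet limit is one ninth of the protocol's own figure for thrombocytopenia, or one tenth of 100000 if a zero was lost, and no other criterion covers the gap. That the limit is far too low for this regimen is well supported by the document. That it is a typing error is likely but remains an inference, resting on the exact white-cell match and the single missing zero.

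The consequence is for patient safety only. How many patients it would affect is unknown, because the protocol gives no baseline platelet distribution; candidates with such counts may be rare.

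**What to change.** In Exclusion Criteria, raise the platelet limit to at least < 90000 cells/µL, which matches the Adverse events review, or to < 100000 cells/µL if the clinical team confirms that a zero was dropped.

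The cost is one number in the eligibility list. Some otherwise eligible patients may be turned away at screening; how many cannot be estimated from the protocol. The planned total of 60, the calculation of at least 25 per arm and the primary t-test stay as they are.
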